### Data analysis

Data from the quantitative assessment of feasibility will be presented using simple descriptive statistics (e.g. means, standard deviations, proportions, change scores, and confidence intervals).

Qualitative data collected to inform feasibility will be thematically analysed and coded using NVivo 12 software (QSR International). This includes interviews with healthcare staff, open-ended questions on the feasibility questionnaires, notes made during feasibility assessment, and notes made by researchers following motivational interviews. Additionally, participant goals will be coded into categories according to what type of behaviour they are targeting, the physical function status of the patient with whom they were created, and more, to create a framework of goals achievable by those with differing degrees of mobility. A combination of deductive and inductive coding will be used depending on the data source; for example, participant goals will be deductive, and open-ended questions inductive.

Exploratory analyses of outcome data will be conducted using IBM SPSS Statistics 25.0. These will comprise of ANCOVA analyses for the measures taken only at baseline and pre-surgery and 2 × 3 ANCOVAs for the data collected at all three timepoints to explore the variance in between-group differences and within-group change scores. We will not formally test for the significance of these differences but will report the mean differences (within and between groups) with 95% confidence intervals.

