**Methods/design:**

The study will be a randomised controlled feasibility trial design, with 2:1 randomisation into an intervention and usual care group respectively. A target of 45 patients aged 60 years or older waiting for elective hip and knee replacements will be recruited from Russells Hall Hospital, Dudley, UK, approximately 8–10 weeks before surgery. The intervention, informed by Self-Determination Theory (SDT), will be composed of multiple behaviour change techniques, namely, motivational interviewing, feedback on current objectively measured sedentary behaviour and activity, goal-setting, environmental modification, self-monitoring, and social support. Assessments will occur at baseline, 1 week pre-surgery, and 6 weeks post-surgery. The primary outcome will be the feasibility of intervention delivery and of the trial procedures, assessed quantitatively based on rates of recruitment, retention, measures-completion, and intervention fidelity assessment, and with mixed-methods assessment of acceptability, practicality, adaption, satisfaction, and safety. Exploratory outcomes will include physical function, cardiometabolic biomarkers, measurement of SDT constructs, and both objective and subjective measurement of physical activity and sedentariness. The study will last up to 18 weeks per participant. No formal between-group comparisons are planned, but the variance in within-group changes and differences between groups in outcome measures will be explored and reported with 95% confidence intervals.

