
#### Intervention structure and delivery

Participants will receive up to five visits (Table 2). The usual care group will attend only three visits, namely, 1, 4, and 5, which are assessment-only visits. The intervention group, however, will also attend visits 2 and 3 (which may be combined if time permits). Visit 2 consists of the motivational interview, whereas visit 3 involves the goal-setting, environmental modification, scheduling of the phone calls, and provision of the pedometer. The intervention is designed to be non-burdensome to researcher and patient in order to make it realistically implementable in orthopaedic care, as the motivational interviewing, education, goal-setting, and environmental modification session can be delivered within a single 90–120-min session, with the addition of three 10-minute phone calls.

**Table 2 Tab2:** Standard Protocol Items Recommendations for Interventional Trials (SPIRIT) diagram to show the participant schedule, including enrolment, allocation, interventions, visits, and assessments [20]

	Study period										
	Recruitment	Baseline	Allocation	Post-allocation							Close-out
Visit	Pre-enrolment	Visit 1	Allocation between visit 1 and 2	Visit 2	Visit 3	PC 1	PC 2	PC 3	Visit 4	Visit 5	Post-study
Timepoint (weeks)	1	2	3	3	3	5	7	9	1 week prior to surgery	6 weeks post-surgery	
Study member	Research nurse	R	Third party	R	R	R	R	R	R	R	R
Enrolment											
Eligibility screening	X										
Informed Consent		X									
Allocation			X								
Study groups											
Sedentary behaviour reduction	X	X	X	X	X	X	X	X	X	X	
Regular care	X	X	X						X	X	
Assessments											
Feasibility (study statistics)											X
Feasibility (interviews with research nurses)											X
Feasibility (questionnaire, acceptability, practicality, adaption, satisfaction, safety)									X	X	
Socio-demographic questions (age, gender, ethnicity, prior occupation, country of origin, educational level, pet ownership, marital status, living arrangements, alcohol frequency smoking frequency, medication info, medical history)		X									
activPAL measurements (sitting time, sit-to-stand transitions, no. of sedentary bouts ≥ 30 mins, avg. length of sedentary bouts, stepping time, standing time, steps per day)		X							X	X	
International Physical Activity Questionnaire–Short Form (IPAQ-SF) [39]		X							X		
Measure of older adults’ sedentary behaviour (MOST) [40]		X							X	X	

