
The measurement timepoints are listed in Table 2, and the rationale for these measures can be read in Additional file 7. These data will inform the design of a definitive trial by helping to identify which outcomes are feasible, which demonstrate the greatest responsiveness to the intervention, and what sample size is needed to provide sufficient statistical power to detect changes in the primary outcome (calculated from standard deviations for changes in the outcome measures). Data will be retained and analysed on an intention-to-treat basis.

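### The 2 × 3 ANCOVA counts pre-allocation baseline as an outcome level: its group term, if reported, is two-thirds of the mean follow-up effect, and a classical GLM fit would also drop usable pre-surgery data

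*Protocol article*

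**What the plan says.** The Data analysis section of the protocol article assigns two models according to how often an outcome is measured. Outcomes measured twice get "ANCOVA analyses for the measures taken only at baseline and pre-surgery". Outcomes measured three times get 2 × 3 "ANCOVAs for the data collected at all three timepoints to explore the variance in between-group differences and within-group change scores". No significance tests are planned; the authors "will report the mean differences (within and between groups) with 95% confidence intervals". On software the section says only "Exploratory analyses of outcome data will be conducted using IBM SPSS Statistics 25.0". It names no covariate, no contrast to be reported and no SPSS procedure.

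The three timepoints are fixed in the Abstract: "Assessments will occur at baseline, 1 week pre-surgery, and 6 weeks post-surgery". Table 2 (Intervention structure and delivery) places randomisation after the first of these: "Allocation between visit 1 and 2". The same table shows SPPB and activPAL at all three visits, and the blood biomarkers at baseline and pre-surgery only.

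The text closing the Exploratory outcomes section gives the purpose: to learn which outcomes are feasible and most responsive, and to size the definitive trial from SDs of change. It adds: "Data will be retained and analysed on an intention-to-treat basis".

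**The concern.** A group-by-time model with three levels treats baseline as an outcome. Because baseline precedes allocation, its expected group difference is zero, and any group effect averaged over the three levels is pulled towards zero by that level. Making baseline the covariate as well, as the word ANCOVA suggests, does not help: baseline is then regressed on itself, and its adjusted group difference is zero by construction.

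At stake is the comparison the exploratory analysis is meant to support. The Aims name SPPB, cardiometabolic biomarkers and objectively measured sedentary time as the candidates. The first and third fall under the three-level model, the biomarkers under the two-timepoint model. Reading a group effect off each model would put the candidates on different scales.

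The second issue is missing visits. A classical repeated-measures GLM needs every level to be present. A participant seen before surgery but not after would drop out of the visit 4 comparison too, although the plan says data are retained.

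**Working it through.** The plan gives no figure for this model. Its one calculated number, the 44 for estimating retention, plays no part here.

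**Inputs from the article:** three visits with baseline before allocation (Abstract, Table 2); 45 participants split 30:15, and 80% expected retention (Sample size). **Assumed for illustration, because the article gives no values:** a true effect of 0.50 SD at both follow-ups, a between-visit correlation of 0.6 and, in one missing-data scenario, a further 10% of participants without visit 5.

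**1. The group term.** Let d1 and d2 be the group differences at visits 4 and 5.

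- Over three levels: (0 + d1 + d2)/3.
- Over the two follow-ups: (d1 + d2)/2.
- Ratio: (1/3)/(1/2) = 2/3, however the effect divides between the visits.

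Relative to the pre-surgery effect d1 alone, the three-level term is 67% if d2 = d1, 50% if d2 = d1/2 and 33% if d2 = 0.

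**2. Simulation (4,000 trials, 30 v 15, complete data, true effect 0.50 SD).**

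| Estimate | Mean (SD units) | Spread across trials |
|---|---|---|
| Group term, three levels, no covariate | 0.34 | 0.27 |
| Group term, three levels, baseline also covariate | 0.34 | 0.14 |
| Baseline-adjusted difference, visit 4 | 0.50 | 0.25 |
| Baseline-adjusted difference, visit 5 | 0.51 | 0.26 |
| Group difference in change, baseline to visit 4 | 0.50 | 0.28 |

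Only the averaged group term is diluted. In the second row the estimate and its standard error shrink together: multiplying by 3/2 gives 0.337 × 1.5 = 0.505 with spread 0.140 × 1.5 = 0.210, and the ratio of estimate to spread is unchanged (about 2.4). There the harm is to the reported size of effect and interval, not to the signal relative to noise.

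**3. Comparability.** Take two outcomes with the same true effect of 0.50 SD. A biomarker analysed by baseline-adjusted ANCOVA at visit 4 would show about 0.50. SPPB read from the three-level group term would show 0.50 × 2/3 = 0.33.

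**4. Missing visits, if a complete-case GLM is used.**

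- 20% lost, the same people at both visits: 45 × 0.8 = 36 (24 + 12) under either method, so nothing is lost by deletion.
- 20% missing each visit independently: complete cases 45 × 0.8 × 0.8 = 28.8, about 29. At least one follow-up: 45 × (1 − 0.2 × 0.2) = 43.2, about 43.
- 20% without visit 4 or 5 and a further 10% without visit 5 only (assumed): 36 have visit 4, but 45 × 0.7 = 31.5 are complete. The visit 4 standard error rises from 0.287 to 0.309 SD in simulation, about 8%; the sample sizes alone give √(36/31.5) = 1.07.

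**The case against.** A reader might infer that the plan will report effects diluted by a third, that the definitive sample size will be wrong as a result, and that the model contradicts the intention-to-treat statement. The article supports none of these as stated.

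- **Dilution.** It never says the averaged group term is the estimate. It speaks of change scores and of mean differences within and between groups, which can be read from per-visit or group-by-time contrasts of the same 2 × 3 layout, and those are unbiased. This stands: the dilution depends on which contrast is reported.
- **Sample size.** This is to come from SDs of change, which do not depend on whether baseline is a level of the model. This stands in full.
- **Intention to treat.** Listwise deletion belongs to one SPSS procedure, and no procedure is named. SPSS MIXED can fit the same layout and keep partial data, and such details are commonly left to an analysis plan. This stands: the conflict is possible, not established.
- **Scale of the missing data.** Visit 4 falls in the last week before surgery, so surgery cancelled earlier would usually mean no visit 4 either. Visit 4 without visit 5 needs a late cancellation, later drop-out, or entry too near the end of the study: Trial status closes recruitment in January 2019 and the study in April 2019, against 15–18 weeks of participation. The group affected may be small.
- **Importance.** The primary outcome is feasibility, and no progression criterion rests on an ANCOVA result. This stands and limits the severity.

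What remains is that the stated model has a pre-allocation outcome level, and the text does not steer the analyst or reader away from the diluted term.

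**Conclusion.** The point holds in a limited form. That baseline is one of three outcome levels is stated in the plan, not inferred from silence. If the group term is reported, it is two-thirds of the mean follow-up effect. This is algebra and needs no assumption beyond randomisation after baseline. Outcomes measured three times would then appear less responsive than those measured twice. Per-visit differences, change contrasts and SDs of change are sound as planned.

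The loss of visit 4 data arises only if a complete-case repeated-measures GLM is fitted. Its size rests on assumed missingness: no loss if the same people miss both visits, 36 down to 31.5 under the further 10% assumption, and 29 complete cases against 43 with some follow-up if 20% miss each visit independently.

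Severity is moderate to low. The analysis is exploratory and untested, and it decides no progression criterion. It is still worth changing, because with no tests planned the estimates and intervals are all that this analysis produces.

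**What to change.** Replace the 2 × 3 ANCOVA by a likelihood-based linear mixed model (SPSS MIXED) along these lines:

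- Outcomes: the values at visits 4 and 5. Baseline enters only as a covariate.
- Fixed effects: group, visit, group × visit, baseline, and baseline × visit, with the two visits allowed to correlate within participant. A covariate for joint (hip or knee) is optional.
- Report: the baseline-adjusted group difference with 95% CI separately at visit 4 and visit 5. Keep within-group changes and their SDs as descriptive summaries for each visit.
- Population: everyone randomised with at least one follow-up value, analysed in the allocated group. State that this relies on missing visits being explainable by the observed data, and give the number contributing at each visit.
- For outcomes measured twice, name baseline as the covariate, so that all candidates can be compared on the same baseline-adjusted visit 4 scale.

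The cost is a change of wording. Data, visits and software stay the same.

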### Progression to a definitive trial

Progression to a definitive trial will be considered if the following metrics are met:A minimum of 75% of patients have their surgeries within 10 days of the 4–8-week intervention window between visit 3 and visit 4.Rate of uptake meets or exceeds 10%.Participant retention rate exceeds 75% between baseline and pre-surgery visits.Study satisfaction must be ≥ 4/5, and risk of harm should be < 2/5, as assessed by the feasibility questionnaire given to participants.The frequency of adverse events does not call into question the safety of the trial as determined by the medical expert on the study ([name]).

The rationale for these criteria is as follows:Participants need to have their surgery within a specific timeframe to keep the intervention length somewhat equivalent. This may be alleviated if a definitive trial was multisite.Based on advice from clinicians, approximately 300 patients are likely to be eligible to be sent a PIS over the 12-month recruiting period. An uptake rate of 10% would be below the target of 45 but would inform us that a multisite strategy would be necessary for the definitive trial.A high number of drop-outs would inform us that the intervention is not acceptable in its current form. The post-surgery visit (visit 5) is not used as a criterion here, as whether patient surgeries are cancelled or delayed is unlikely to be related to study procedures.The study should be perceived as safe and acceptable by participants.Safety should be of primary concern, as increased walking and standing could potentially increase the risk of falls in this population.

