### Sample size

A power calculation informed us that a sample size of 44 is sufficient to allow estimation of the retention rate of a future clinical trial with 95% confidence intervals of ± 11%, given an expected retention rate of 80%. For this reason, this study aims to recruit 45 patients, with 30 randomised to the intervention group and 15 to the usual care group. This sample size is also consistent with advice from clinicians about expected uptake rate and sample sizes used in prior feasibility studies to reduce sedentariness in older adults [11] This sample will be recruited over a 12-month period.

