Quality of life (QoL) (EuroQoL 5D-5L, EuroQoL Visual Analogue Scale) [41]		X							X	X	
Oxford Hip and Knee Score(s) [42, 43]		X							X	X	
Basic Psychological Needs Scale [25, 26]		X							X	X	
Activities of daily living (ADL) (Katz-ADL) [37]		X							X		
Physical function–Short Physical Performance Battery (SPPB) [36]		X							X	X	
Short Form Mini Nutritional Assessment (SF-MNA) [37]		X									
Weight		X							X	X	
Height		X									
Body mass index		X							X	X	
Waist-to-hip ratio		X							X		
Albumin, high-density lipoprotein, low-density lipoprotein, cholesterol, triglycerides, vitamin D, cortisol, transferrin, HBA1c, CRP, full blood count		X							X		

*R* researcher, *PC* phone call, *CRP* C-reactive protein

Due to the variation in surgery scheduling and the difficulty in obtaining accurate surgery dates months in advance, not all participants may undergo the same duration of intervention. The intervention is intended to be of 6-weeks’ duration but can be extended or shortened where required. Individuals will receive visit 4 in the week leading up to their surgery and will receive visit 5 6-weeks post-operatively. Most individuals are expected to have surgery 4–10 weeks after visit 3. Participants are expected to participate in the study for a total of 15–18 weeks. The variability in intervention delivery and timings will be recorded to help inform the assessment of study feasibility.

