#### Secondary outcome assessment

##### Feasibility questionnaire

Feasibility will be assessed secondarily by the use of bespoke questionnaires that comprise both open and closed questions: one for the usual care and one for the intervention group. Each question is designed to target an aspect of feasibility based on guidance by Bowen et al. [35]. The questionnaires assess acceptability, practicality, adaption, satisfaction/feedback, and safety/risk for the participant. These files are available as Additional files 4 (usual care) and 5 (intervention).

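### The satisfaction and perceived-harm progression criterion is scored only from participants who reach visit 4, so early leavers and those whose surgery is cancelled or indefinitely delayed give no score

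*Protocol article*

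**What the plan says.** Under Progression to a definitive trial, the fourth of five criteria requires satisfaction of at least 4/5 and risk of harm below 2/5, "as assessed by the feasibility questionnaire given to participants". Its rationale is that "The study should be perceived as safe and acceptable by participants".

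The questionnaire has two versions, "one for the usual care and one for the intervention group" (Feasibility questionnaire). In Table 2, the row beginning "Feasibility (questionnaire, acceptability, practicality, adaption, satisfaction, safety" is marked at visits 4 and 5 and nowhere else. On timing, the text below Table 2 says: "Individuals will receive visit 4 in the week leading up to their surgery and will receive visit 5 6-weeks post-operatively".

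The third criterion is "Participant retention rate exceeds 75% between baseline and pre-surgery visits". Its rationale takes a high number of drop-outs as evidence that the intervention is not acceptable as it stands. Feasibility (study statistics) defines retention as still providing measures at a timepoint, and lists indefinitely delayed or cancelled surgery as an outcome to be counted. The article describes no questionnaire or contact at withdrawal for the satisfaction and harm items.

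**The concern.** The criterion is meant to show how participants in general see the study, but its score comes only from those who get as far as visit 4. The intervention is delivered between allocation and visit 4, so a person who leaves the study during it because it felt burdensome or unsafe is not asked. Because the protocol links drop-out to unacceptability, the chance of a missing score is plausibly related to the score itself. The likely direction is favourable to progression, with satisfaction too high and perceived harm too low.

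A second group is also unasked. Visit 4 is tied to the surgery date, so participants whose surgery does not take place may never have it. Their views need not be unfavourable, and they should be kept apart from withdrawals.

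**Working it through.** The plan gives no figure for how many participants will be asked, so there is none to reproduce. The precision statement in Sample size plays no part here.

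**Inputs from the protocol article**
- Target of 45 participants, 30 intervention and 15 usual care (Sample size).
- Planning assumption: "given an expected retention rate of 80" per cent (Sample size).
- Retention to the pre-surgery visit must exceed 75%; satisfaction must be at least 4 and harm below 2 (Progression to a definitive trial).

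**How many can be unasked.** This counts everyone without a visit 4 as not retained.
- Lowest passing retention: 33/45 = 73.3% fails and 34/45 = 75.6% passes, so 45 − 34 = 11 are unasked.
- Expected retention: 0.80 × 45 = 36, so 45 − 36 = 9 are unasked.
- The retention criterion is not stated by arm. If all 11 losses fell in the intervention arm, 19/30 = 63.3% of that arm would answer and retention would still pass.

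**What this could do to the score.** Three assumptions are needed: the criterion is a mean on a 1–5 scale (the article does not name the statistic), all 45 should count, and the unasked would have given the scores shown. No document gives a score for people who leave.

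Overall mean = (asked × asked mean + unasked × unasked mean) / 45.

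| Asked / unasked | Satisfaction, asked mean 4.0; unasked 1, 2, 3 | Harm, asked mean 1.9; unasked 3, 4, 5 |
|---|---|---|
| 34 / 11 | 3.27, 3.51, 3.76 | 2.17, 2.41, 2.66 |
| 36 / 9 | 3.40, 3.60, 3.80 | 2.12, 2.32, 2.52 |

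Examples: (34 × 4.0 + 11 × 2)/45 = 158/45 = 3.51; (36 × 1.9 + 9 × 3)/45 = 95.4/45 = 2.12.

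These cases put the asked mean at or close to the threshold. With more room, the result depends on who is missing. Take 35 asked (35/45 = 77.8%), with asked means of 4.2 for satisfaction and 1.6 for harm:
- All 10 unasked are unfavourable (2.5 and 3.5): satisfaction (35 × 4.2 + 10 × 2.5)/45 = 3.82 and harm (35 × 1.6 + 10 × 3.5)/45 = 2.02. Both fail.
- Five of the 10 are surgery cancellations with average views and five are unfavourable: satisfaction (40 × 4.2 + 5 × 2.5)/45 = 4.01 and harm (40 × 1.6 + 5 × 3.5)/45 = 1.81. Both still pass.

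So the thresholds can be crossed at drop-out levels that the plan accepts, but this depends on the scores assumed and on how many of the unasked are true withdrawals.

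**The case against.** The strongest reply is that the plan does not leave acceptability to this criterion alone. All five criteria are to be met, drop-out has its own criterion with an acceptability rationale, and adverse events have another. Progression will then be considered, which is less than an automatic rule. This stands as a partial offset. It does not close the gap: retention counts leavers without recording what they thought, and adverse-event review does not measure perceived harm. The intention-to-treat statement cannot supply scores that were never collected.

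A reader might infer that leavers' views go wholly unrecorded. The documents do not support that. Both arms are telephoned about every two weeks, intervention participants can note problems in the booklet, and researchers' notes are analysed thematically. These sources can show burden or worry before someone leaves, but they yield no score for this criterion.

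A reader might also infer that only those who finish the whole study are asked, or that anyone who gives up the goals is missed. Neither is right. A person who leaves after visit 4 has been asked once, and a person who stops the goals but attends visit 4 is asked.

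Finally, this is a condensed article. The full protocol and the questionnaires in the additional files are not shown, and an exit procedure could be described there. The point is limited to the published schedule and criterion.

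**Conclusion.** The point holds as a weakness in how one progression criterion is measured. From the schedule alone, 9 of 45 participants at the expected retention, and 11 of 45 at the lowest passing retention, give no satisfaction or harm score. A favourable bias is probable, because the protocol itself treats drop-out as a sign of unacceptability. Its size is unknown.

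It would go too far to say that the progression decision will be wrong or that the thresholds would flip. Every leaver's score above is assumed, and in the milder case both thresholds are still met (4.01 and 1.81). Some of the unasked will be surgery cancellations or delays, which the protocol considers unlikely to be related to study procedures. About a third of participants are in usual care, with no intervention to find burdensome. The change is worth making because it is cheap and the score feeds the decision on a definitive trial.

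**What to change.** 1. Offer the closed satisfaction and harm items of the existing questionnaires, by phone or post and voluntarily, to participants who leave before visit 4 or whose visit 4 cannot take place.
2. Judge the criterion on everyone with a response.
3. Report by arm how many did not answer and why they left, separating withdrawal from cancelled or delayed surgery.
4. As a sensitivity analysis only, show the result with unfavourable scores for withdrawals who did not respond. Surgery cancellations should be left out of this. As a decision rule it would be too severe: with 10 non-responders set to 1, the other 35 would need a mean of (45 × 4 − 10 × 1)/35 = 4.86.

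The cost is a short contact with roughly 9–11 people, and some will not respond. Trial status gives recruitment from January 2018 to an expected end in January 2019, with completion in April 2019. For participants who have already left, only the reporting and the sensitivity analysis (items 3 and 4) apply, and these need no new data collection beyond the reasons for leaving.
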